## Abstract

**Background:**

Patients with incurable but not-yet-biopsied cancers sometimes require urgent palliative radiation. However, wait-times for biopsy procedures and pathologic results can delay treatment, with significant consequences to patient quality of life and/or the chance of irreversible cancer complications. There is no prospective data to guide empirical decision-making in these urgent, palliative contexts.

**Methods:**

In this prospective single-arm pragmatic clinical trial, we will enrol 48 patients with incurable cancer where a biopsy is delaying urgent palliative radiation. Patients will receive empiric upfront palliative radiation without biopsy-confirmation. The primary endpoint is the rate of inappropriate radiation, defined when the patient’s biopsy shows a non-malignant entity or a malignancy that is better treated upfront with systemic therapy (or therapy other than radiation). Secondary endpoints include: histologic diagnostic accuracy, molecular testing accuracy, biopsy complications rates, evidence of radiation effect in biopsy, time from enrolment to radiation/biopsy, and Edmonton Symptom Assessment Scale (ESAS) scores. Patients are eligible only if the probability of incurable malignancy is deemed > 95% and the risk of lymphoma < 20% by the treating physician, based on clinical examination and imaging investigations.

**Discussion:**

This study will provide prospective data to guide oncologists and patients in making informed decisions when weighing the competing risks of delaying palliative radiation versus treating without pathologic confirmation.

**Trial registration:**

*ClinicalTrials.gov* Identifier: NCT06156800. Date of registration: December 5, 2023.

## Background

In palliative radiation oncology, there is often a dilemma between the urgency of starting radiation treatment versus waiting for a biopsy for definitive diagnosis. Clinicians typically prefer waiting for a biopsy to confirm a malignancy prior to radiation, due to perceived risks of incorrect management (i.e. radiating a lymphoma or non-malignant lesion) and the possibility of radiation resulting in a non-diagnostic biopsy.

With increasingly stressed healthcare systems globally, biopsy wait times have lengthened, with the consequence of significantly delaying palliative radiation, sometimes by over a month in Canada. This comes at a high cost for patients, as their disease and symptoms continue to progress during the waiting period. Wait times for treatments have been associated with patient and caregiver anxiety, depression and poor quality of life [1].

Modern decision-making for patients in a palliative context requires a more nuanced balance of competing priorities for the patient, while taking into account the new realities in a publicly-funded healthcare system. Since dose/fractionation schemes for palliative radiation usually do not depend on the specific tumour histology, in some cases, physicians will elect to deliver radiation prior to biopsy, as part of shared decision making with the patient. However, to our knowledge, this approach has not been prospectively studied. RT-NOW is a single arm pragmatic trial with the goal of prospectively assessing this approach of delivering radiation before biopsy when warranted by symptom urgency, in carefully selected patients.

There are 4 main issues that clinicians are hoping to avoid when treating without a pathologic diagnosis:

Creating a non-diagnostic biopsy through radiation effects on tissue.Increasing the risk of biopsy complications.Treating a non-cancerous process.Treating a cancer that would be best managed with chemotherapy/systemic therapy as the primary treatment (i.e. lymphoma, small cell lung cancer, germ cell tumor).

### Potential issue #1: creating a non-diagnostic biopsy through radiation effects on tissue

Non-diagnostic biopsies can mean either absence of histological or molecular testing results. We estimate that the risk of histologic non-diagnostic biopsies at a recently irradiated site is low (i.e. < 5%), if done within 2–4 weeks of starting radiation [2, 3]. In a study of the histologic remission of nasopharyngeal carcinoma (known to be a radiosensitive tumor), serial biopsies were taken weekly after a definitive course of radiation (median 61 Gy in 35–40 fractions). Fewer than 5% of patients had histologic remission 1 week after completion of radiation, corresponding to at least 8 weeks after radiation initiation [2]. In the Stockholm III trial for rectal cancer, the rates of pathologic complete response from surgery shortly (1–7 days) after short-course radiotherapy (RT) (25 Gy in 5 fractions) was 2.1%. Without any additional radiation, waiting 4–8 weeks after completion of radiation yielded a pathologic complete response rate of 11.8% [3]. In the MISSILE trial for early-stage non-small cell lung cancer (NSCLC) treated with stereotactic ablative radiotherapy (SABR), even 10 weeks after high-dose treatments, 40% of patients still had viable tumor cells by hematoxylin & eosin (H&E) staining [4].

Given these results, we postulate that the risk of a negative biopsy after radiation is likely overestimated by clinicians. In patients where a biopsy is obtained within weeks of palliative-dose radiation, we estimate the probability of a non-diagnostic biopsy as < 5%. The caveat is that though there is available data on the effects of radiation on histologic diagnosis, there is a lack of available data on the effects of radiation on molecular tests (i.e. EGFR, ALK, BRAF, etc.). This study will actively assess for the diagnostic quality of both immunohistochemical and molecular testing on biopsies of irradiated sites.

### Potential issue #2: increasing the risk of biopsy complications

Based on available literature, the risks of increased biopsy complications from a recently irradiated site are likely < 1% [5]. In a review of diagnostic biopsies performed in irradiated tissue, only 17 of 2160 patients were reported to have biopsy complications [5]. In this review, most studies did not actively evaluate for biopsy complications and relied on either chart review or patient reporting, as such, the study might underestimate the rates of low-grade complications. We will actively evaluate for biopsy complications of irradiated sites in our study.

### Potential issues #3 and 4: treating a non-malignant process or a malignancy in which upfront radiation would have been inappropriate

These two issues have historically been the main reasons for delaying radiation before the biopsy result is available, as they may either lead to unnecessary treatment and toxicity for a patient, or in the worst case, limit the ability to deliver curative-dose radiotherapy in the future (i.e. lymphoma). With modern imaging techniques (i.e. cross-sectional imaging and sometimes functional imaging), we believe clinicians are able to attain a high certainty of malignancy without a biopsy in certain settings. In these urgent palliative situations, there may be an inherent risk to delaying radiation, therefore physicians and patients should discuss the diagnostic probability of malignancy, the potential risks of upfront radiation as well as the possible consequences of delaying radiation. Ultimately, the physician and patient must come to a shared decision on whether upfront radiation is appropriate and in keeping with the patient’s clinical situation, preferences, and values. The data prospectively collected from this trial will hopefully better inform future physicians and patients on these risks.

## Methods

### Objective

To determine if it is safe and feasible to deliver palliative radiation before a biopsy result is available in a carefully selected group of patients with urgent indications for radiation.

### Study design

This is a prospective, single arm pragmatic clinical trial assessing the feasibility of delivering palliative radiation before a biopsy result is available in patients with urgent indications for palliative radiation. Study schema is shown in Fig. 1. Participants will be enrolled by study personnel at each institution before delivery of radiation. Elements from PRECIS-2 were used to inform our pragmatic trial design [6, 7]. For example, we kept the eligibility broad across cancer types, with no required performance status scores, only one mandated follow up and no additional recruitment efforts beyond usual care.

**Fig. 1 Fig1:**
[figure not shown]
General study schema

We hypothesize that with a radiation-before-biopsy approach, the rate of “inappropriate radiation” will be 5% or less. We hypothesize that the biopsy yields to establish a histologic and molecular diagnosis will be acceptable and comparable to our institutional averages of 90–95% and 80–90%, respectively. We hypothesize that the rates of complications will be acceptable and comparable to our institutional average of 5–10%.

### Study endpoints

#### Primary endpoint

Rate of “inappropriate use of radiation”, defined as the percentage of patients in whom management would have differed if the biopsy results were known prior to radiation. These cases meet the definition either when:
Biopsy pathology clearly shows a non-malignant entity.Or the biopsy shows malignancy, but the patient would have received upfront systemic therapy or an alternate therapy, rather than radiotherapy, had the biopsy results been known.

#### Secondary endpoint

Histological diagnostic accuracy, defined as the percentage of biopsies that yielded a histological diagnosis. This will include a comparison of diagnostic yield between biopsies done at radiated vs. non-radiated sites.Molecular testing accuracy, defined as the percentage of biopsies that yielded enough viable tissue for successful Next-Generation Sequencing testing using the ThermoFisher Oncomine V3 panel.Number of biopsy attempts required.Biopsy complication rates.Time from enrollment to first fraction of radiation.Time from enrollment to biopsy.Evidence of radiation effect in biopsy, defined as evidence of necrosis or dense fibrosis causing non-diagnosis in a lesion that had been radiated before the biopsy. If a biopsy was non-diagnostic because it was non-lesional, it would not be considered non-diagnostic as a result of radiation.Overall survival, defined as the time from enrollment to death from any cause or date of last follow-up, whichever occurs first.Edmonton Symptom Assessment Scale (ESAS) quality of life scores before RT and at first follow up (i.e. 4 weeks after RT).

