#### Biopsy

Biopsies should be taken at whichever site is clinically preferred, typically the most anatomically feasible site of biopsy (regardless of whether it has been irradiated), considering institutional wait times and availability for different biopsy procedures. If the first biopsy attempt is unsuccessful, the second attempt can be a repeat biopsy at the same site or at another site.

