### Adverse events

We will not be routinely evaluating for adverse events from radiation since these patients are receiving radiation regardless of enrolment (the trial is simply studying the *timing* of radiation in relation to biopsy).

However, we will actively evaluate for biopsy complications as it is possible that the frequency or severity of biopsy complications could increase if done within an irradiated area. In the follow-up visit post-treatment questionnaire, we will specifically evaluate for the following complications:

Pneumothorax (requiring a chest tube).Wound infections (requiring antibiotics).Prolonged bleeding from biopsy site.Fistula formation.Delayed wound healing, defined as non-healing wound or dehiscence at biopsy site > 6 weeks following the biopsy (requiring a specialist wound care team or continued antibiotics) – this should be assessed from the chart and included in post-treatment questionnaire.

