### Statistics and sample size calculations

We hypothesize that the primary endpoint, rate of “inappropriate radiation”, will be no more than 5%. We consider it unacceptable if the rate of “inappropriate radiation” is ≥ 20%. Using a one-sided, one-sample binomial test, with 90% power at the 5% significance level, to reject the null hypothesis of a change rate of ≥ 20%, with 10% drop-out, we estimate that 48 patients are needed.

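### Complications and molecular yield are not split by whether the biopsied tissue had been irradiated, so a radiation effect can be diluted into the institutional benchmark range

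*Protocol article*

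**What the plan says.** All references are to the protocol article.

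- **Aim, complications.** Potential issue #2 states: "We will actively evaluate for biopsy complications of irradiated sites in our study". Adverse events gives the reason for collecting them: "it is possible that the frequency or severity of biopsy complications could increase if done within an irradiated area".
- **Aim, molecular testing.** Potential issue #1 says data on how radiation affects molecular tests are lacking, and that the study will assess this in biopsies from irradiated sites.
- **Endpoints.** Under Secondary endpoint, histological yield carries a comparison of radiated and non-radiated sites. Molecular testing accuracy is a percentage of biopsies, with no split. Complications are listed only as "Biopsy complication rates".
- **Benchmarks.** The hypotheses under Study design expect complications to be "comparable to our institutional average of 5–10" per cent and molecular yield to match an institutional 80–90%. Neither is tied to irradiated tissue.
- **Which biopsies enter.** The Biopsy section allows the most feasible site, "regardless of whether it has been irradiated". Timing of biopsy and radiation lets the biopsy precede radiation, and even enrolment, if the result is still pending.
- **Analysis.** Data analysis refers to overall rates for yield and complications.
- **Interim.** Planned safety interim analysis, repeated in the section on radiation to the only available biopsy site, sets a 70% molecular-yield threshold for patients whose only feasible biopsy site was irradiated. It sets none for complications.

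**The concern.** The question is about tissue that has been irradiated, but the two endpoints meant to answer it are written over all biopsies. Some of those biopsies will carry no radiation exposure, and they pull the pooled rate towards the usual institutional rate, which is also the yardstick. A pooled result inside 5–10% could thus be read as reassuring while the irradiated-site rate lies well above it. The same applies to molecular yield, which the protocol itself names as the evidence gap.

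Risks to subjects says each named risk will be measured to judge whether this approach is acceptable as standard care. Two of the four risks listed there, non-diagnostic tissue (through its molecular part) and biopsy complications, depend on these endpoints.

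**Working it through.** **The plan's own figure.** The only sample size stated is 48, for the primary endpoint: "Using a one-sided, one-sample binomial test, with 90% power at the 5% significance level". The null rate is 20% and the expected rate is 5%. The smallest exact design is n = 44: reject at 4 or fewer events, exact alpha 0.0440, power 0.9325. For 10% drop-out, 44 × 1.1 = 48.4, or 44 / 0.9 = 48.9. So 48 reproduces to within one patient. No figure is given for complications or molecular yield, so 48 is simply the most patients available to them.

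**Inputs for the dilution check**
- From the protocol: upper complication benchmark 10%; lower molecular benchmark 80%.
- Assumed: complications in unexposed tissue 5% (low end of 5–10%), with 7.5% as a variant; molecular yield in unexposed tissue 90% (high end of 80–90%), with 85% as a variant; one biopsy per patient.
- Not given: the share f of biopsies from tissue already irradiated. Range shown: 25% to 75%.

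**Formula.** Pooled = f × (irradiated rate) + (1 − f) × (unexposed rate). The irradiated rate at which the pooled value just meets the benchmark is [benchmark − (1 − f) × unexposed rate] / f.

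Examples at f = 0.50:
- Complications: (0.10 − 0.50 × 0.05) / 0.50 = 0.15.
- Molecular yield: (0.80 − 0.50 × 0.90) / 0.50 = 0.70.

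| f | Highest irradiated-site complication rate with pooled ≤ 10% (5% elsewhere) | Same, 7.5% elsewhere | Lowest irradiated-site molecular yield with pooled ≥ 80% (90% elsewhere) | Same, 85% elsewhere |
|---|---|---|---|---|
| 25% | 25% | 17.5% | 50% | 65% |
| one third | 20% | 15% | 60% | 70% |
| 50% | 15% | 12.5% | 70% | 75% |
| 75% | 11.7% | 10.8% | 76.7% | 78.3% |

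**Where dilution does not hide the effect.** At f = 0.75, a tripling from 5% to 15% pools to 0.75 × 15% + 0.25 × 5% = 12.5%, outside the range.

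**Chance of a reassuring observed rate.** Take 24 irradiated and 24 unexposed biopsies with true rates of 15% and 5%. The probability that the observed pooled rate is at or below 10% (at most 4 of 48) is 47%. For the irradiated group alone (at most 2 of 24) it is 28%.

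**What a split can and cannot show.** With 24 versus 24, a two-sided Fisher test at 5% has 11% power for 15% versus 5%, and 24% power for 20% versus 5%. For 80% power, about 141 and 76 biopsies per group would be needed (normal approximation). The split removes the dilution but cannot support a formal test.

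**The case against.** **Pooling is partly inferred.** No sentence says these endpoints will be analysed only in pooled form. This is a condensed article, a by-site table may sit in the full protocol or analysis plan, and the statements about irradiated sites can be read as the intended analysis. The reference to overall rates occurs where the text explains that patients with repeatedly non-diagnostic biopsies stay in the secondary analyses; it does not forbid a split. This stands as a limit on how strongly the point can be put. It does not remove it, because the same endpoint list spells out the exposure comparison for histology and omits it for the other two, and the benchmarks are stated here without a split.

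**A reader might infer that the complication question will go unanswered.** The documents do not support that. The protocol commits to evaluating complications at irradiated sites, and the data to do so should exist. The risk is that the stated endpoint and benchmark give a diluted answer.

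**A reader might also infer that the 5–10% benchmark counts different events from the trial's complication list.** The protocol does not say how the institutional average was defined, so a mismatch cannot be shown. The 17 of 2160 in the cited review does not show one either, since the protocol warns that the review may undercount low-grade events.

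**Molecular yield is not wholly unprotected.** The interim rule looks at irradiated tissue only and carries a consequence. That stands, but it covers only single-site patients, only at the interim, and not complications.

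**The overall rate is legitimate.** It describes the radiation-before-biopsy strategy as a whole. That also stands, so the split should be added and the overall rate kept.

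**Conclusion.** The point holds in a limited form. As written, the complication and molecular endpoints do not match the stated irradiated-site aims, and the unsplit benchmarks allow dilution. The size depends on an exposed share the protocol does not give. With 5% complications elsewhere, irradiated-site rates from 11.7% (three quarters exposed) to 25% (one quarter exposed) would still pool to no more than 10%. With 90% molecular yield elsewhere, irradiated-site yields from 76.7% down to 50% would still pool to at least 80%. These backgrounds are the favourable ends of the stated ranges. At 7.5% and 85% the room for masking shrinks, and when most biopsies are exposed it is small. The primary endpoint and the sample size are unaffected. The change is worth making because it bears on two of the risks the trial sets out to measure.

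**What to change.** In the Secondary endpoint list, extend the comparison already specified for histological yield to complications and molecular yield. Classify each biopsy by whether the sampled tissue had already received radiation when it was taken, so that a biopsy of a target lesion before the first fraction counts as unexposed. Report both groups with exact confidence intervals beside the overall rate. Under Study design, state that the 5–10% and 80–90% benchmarks will be read against the irradiated group as well as overall.

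The cost is wording and extra table columns. Existing endpoints already call for biopsy site relative to radiation and for the timing of the biopsy and the first fraction. The downside is smaller denominators and wide intervals. The comparator is also non-randomised, since the biopsy site is chosen on clinical grounds and the groups may differ in procedure and baseline risk. The text should therefore call the comparison descriptive.

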### Patient selection

#### Inclusion criteria

Age 18 years or older.Willing to provide informed consent.Palliative treatment intent: either metastatic or incurable locally advanced disease.Tissue diagnosis is not required for determination of dose/fractionation scheme.Recent cross-sectional imaging (e.g. computed tomography [CT], magnetic resonance imaging [MRI], positron emission tomography [PET]/CT) of the area to be treated, done within the past 3 months.Treating physician considers the pre-test probability of cancer > 95% based on clinical judgement and radiological findings.For patients with a prior history of malignancy, patients should be enrolled only when a biopsy is required for management decision-making. For example, these should be cases where urgent palliative radiation is delayed by the need for a biopsy. Patients can be enrolled, for example, under the following scenarios:
They have a prior malignancy but that prior malignancy is not considered the most likely histology for the current malignant lesion being treated.Re-biopsy of the site being radiated is needed for molecular biomarkers.
Radiation is considered urgent (i.e. patient should receive radiation prior to biopsy date). Urgent indications may include (Table 1):
Spinal cord compression (actual or impending) and inoperable.Symptomatic brain metastasis and inoperable.Other lesions causing neurologic deficit.Pulmonary lesion causing or threatening lung obstruction.Bleeding (including hemoptysis, upper/lower gastrointestinal bleed, hematuria).Superior vena cava obstruction (actual or impending).Cancer-related pain, not adequately responding to analgesia.Impending pathologic fracture.
The patient has at least 1 site of cancer amenable to biopsy.As per standard practices, if the radiation oncologist will be radiating the only site available to biopsy, they should proceed with caution. Patients should only be enrolled on trial if the risk of harm from delaying RT significantly outweighs the risks of possible non-diagnostic tissue. If the patient may potentially be eligible for systemic therapy, the treating radiation oncologist should consult a medical oncologist for an opinion regarding the risks of non-diagnostic molecular testing. The weighing of these priorities should be thoroughly discussed with the patient and the discussion should be documented. Reasons for radiating a patient with a single lesion prior to biopsy include:
Spinal cord compression (actual or impending) and inoperable.Brain metastasis with significant symptoms or neurologic deficits and inoperable.Other lesions causing neurologic deficit.Pulmonary lesion causing or threatening lung obstruction.Uncontrolled bleeding.Superior vena cava obstruction (actual or impending).Limited upside to molecular testing, as determined by the medical oncologist (i.e. patient unfit for available systemic therapies or limited options for systemic therapy).

**Table 1 Tab1:** Examples of urgent indications for palliative radiotherapy

▪ Spinal cord compression (actual or impending) and inoperable
▪ Symptomatic brain metastasis and inoperable
▪ Other lesions causing neurologic deficit
▪ Pulmonary lesion causing or threatening lung obstruction
▪ Bleeding (including hemoptysis, upper/lower gastrointestinal bleed, hematuria)
▪ Superior vena cava obstruction (actual or impending)
▪ Cancer-related pain, not adequately responding to analgesia
▪ Impending pathologic fracture

